#### Secondary outcome measures

Three-dimensional quantification and shear wave elastography (SWE).

Trans-rectal three-dimensional ultrasound (VOLUSON E8) will be used to assess the morphological parameters of the lacunae of the levator hiatus in CP/CPPS patients. The area of the levator hiatus is situated at a depth of 2–4 cm from the perineum, which is well within the effective range of 7–4-MHz transducers. The plane of minimal anteroposterior (AP) diameters will be identified in the mid-sagittal image; at this level, the axial plane will be then utilized to determine the minimum AP and lateral diameters of the levator hiatus as well as the hiatal area. After B-mode sonographic evaluation, shear wave elastography will be activated. Shear wave elastography will be used to assess the modulus of elasticity of the pubovisceral muscle (attaching laterally to the perineum) in patients with CP/CPPS. The propagation velocity of shear waves is proportional to the elastic modulus of tissue. By measuring the velocity of shear waves, the hardness of tissue can be measured directly [30]. The stiffness of the tissue will be displayed in color code rectangle.

(2)Sympathetic skin response (SSR).

SSR is a recently established method of noninvasive somatic neurography that offers the advantages of both non-invasiveness and specificity, using the SA7550 FlexComp Infiniti System (Thought Technology, Canada).

Sympathetic skin responses will be recorded with the active electrodes placed in the left palm and the reference electrodes placed on the dorsum of the left hand while the patient is in the sitting position. A channel recording from the hand will be obtained simultaneously via stimulation of the contralateral median nerve at the level of the wrist with a stimulation intensity of 20 mA for 0.2 ms [31]. Three potentials will be recorded, and the mean values will be used for analysis.

### Harm outcomes

Based on previous studies, transrectal myofascial release therapy has an approximately 15% chance of causing perianal pain, which will self-heal after two treatments and no special treatment is required.

Extracorporeal shockwave therapy has a very low probability of side effects such as edema and capillary rupture and does not require any specific treatment.

If the patient develops any discomfort during the study, or if there are any unexpected circumstances, the therapist will make a judgment and give appropriate medical treatment.

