## Abstract

**Background:**

Chronic prostatitis/chronic pelvic pain syndrome is a highly prevalent syndrome. Previous studies showed that extracorporeal shockwave therapy and myofascial release therapy could improve the quality of life in patients with chronic prostatitis/chronic pelvic pain syndrome (CP/CPPS). Theoretically, combined therapy with extracorporeal shockwave therapy and myofascial release therapy will likely have significant advantages in treating CP/CPPS. We, therefore, present a protocol for conducting a well-designed randomized controlled trial to compare the efficacy and safety of each therapy.

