**Methods:**

The proposed study will be a three-group randomized control trial (RCT) design that includes 150 participants from Zhongda Hospital Affiliated to Southeast University, with equal allocation of participants to the three intervention groups. The study duration will be 8 weeks, which includes a 4-week treatment period and a 4-week follow-up period. The primary outcome will be the changes in surface electromyography (sEMG) assessment and National Institutes of Health-Chronic Prostatitis Symptom Index (NIH-CPSI). The secondary outcomes will include the changes in three-dimensional quantification, shear wave elastography (SWE), and sympathetic skin response (SSR) testing. Assessments will be conducted before the intervention (T0), before the 5th intervention (T1), immediately after the 8th intervention (T2), and the 4th week after the end of the 8th intervention (T3).

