**Fig. 1 Fig1:**
[figure not shown]
Research flowchart

General information, medical/treatment history, and pre-assessment results of each participant will be confidentially collected by the research assistant before the initial intervention.

Assessments will be conducted before the intervention (T0), before the 5th intervention (T1), immediately after the 8th intervention (T2), and at the 4th week after the end of the 8th intervention (T3), which include the surface EMG evaluation of pelvic floor muscles, NIH Chronic Prostatitis Symptom Index (NIH-CPSI), three-dimensional quantification, shear wave elastography, and the sympathetic skin response.

The primary outcome measurements will be performed at T0, T1, T2, and T3. Secondary outcome measurements will be carried out at T0 and T3.

The SPIRIT figure is displayed in Table 1.

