### Plans to promote participant retention and complete follow-up

Once participants are enrolled in the study, the primary investigator will emphasize the importance of regular treatment for recovery. If participants can be evaluated at all stages of the treatment process, it will be free of charge. Funding will be detailed in funding statements. Participants were contacted by telephone 2 weeks after the last intervention to ensure the follow-up 4 weeks after the intervention.

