### Blinding

This study was a double-blinded, randomized, controlled trial. The subjects had no knowledge of the distribution. Therapists will not be involved in collecting data, and data managers will not participate in the intervention of patients.

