This study innovatively uses the modulus of elasticity to assess pelvic floor muscle tone, which has previously been used to assess the muscle status of spastic muscles in hemiplegic patients with good sensitivity [48, 49]. In the course of the previous treatment, it was found that the pelvic floor muscles became less stiff and more elastic after myofascial release therapy, but the improvement in elasticity has not been assessed by objective criteria.

Sympathetic skin response is a transient potential change in the skin that is triggered by endogenous or exogenous stimuli. As a noninvasive test, SSR can be used clinically to detect disorders related to sympathetic tone [50]. Due to the extensive distribution of sympathetic postganglionic fibers in the skin and the fact that the nerves in the skin of the upper limbs and chest originate from the cervical and stellate ganglia, stellate ganglion nerve activity can be reflected by upper limb skin sympathetic nerve activity. Since reduction of CP/CPPS symptoms can significantly improve depression, anxiety, and pain symptoms of patients [16], we presume the possible pathogenesis of chronic pelvic pain syndrome may be the altered sympathetic nerve function caused by anxiety and depression.

This study will compare the agreement between patients’ sympathetic skin response and NIH-CPSI scores at different stages of treatment. If the results of this study show good linear correlations, it may suggest that one of the pathogenic mechanisms of CP/CPPS is hypo- or hyper-autonomic function and that more effective combination treatments could be developed by focusing on this pathogenesis in the future. This proposed study aims to contribute to this growing area of research by exploring the pathogenesis and novel therapeutic targets of CP/CPPS.

Moreover, the study may yield a limitation: we could only realize that participants and evaluators were blinded, and the therapist would know the grouping. We will try to improve our method in the follow-up research, trying to achieve the requirement that therapists be blinded.

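### The protocol announces a safety comparison of the therapies, but no harm variable appears in its outcomes, assessments, collection plan or analysis

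*Protocol article*

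**What the plan says.** The Background paragraph of the abstract gives the purpose as "to compare the efficacy and safety of each therapy". The Methods paragraph of the abstract then lists the outcomes: "The primary outcome will be the changes in surface electromyography (sEMG) assessment and National Institutes of Health-Chronic Prostatitis Symptom Index (NIH-CPSI") and "The secondary outcomes will include the changes in three-dimensional quantification, shear wave elastography (SWE), and sympathetic skin response (SSR) testing". Study design describes the assessments at T0 to T3, "which include the surface EMG evaluation of pelvic floor muscles, NIH Chronic Prostatitis Symptom Index (NIH-CPSI"), followed by the ultrasound, elastography and skin-response measures. Plans for assessment and collection of outcomes schedules these primary and secondary measurements and nothing else. Statistical methods names comparisons of sEMG and NIH-CPSI, plus correlation, mediation and agreement analyses.

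The section Harm outcomes gives about a 15% chance of perianal pain with transrectal myofascial release, resolving after two treatments. It calls shockwave side effects such as edema and capillary rupture very unlikely. It then says: "If the patient develops any discomfort during the study, or if there are any unexpected circumstances, the therapist will make a judgment" and provide treatment. Under Blinding, "Therapists will not be involved in collecting data, and data managers will not participate in the intervention of patients". The Discussion concedes that "we could only realize that participants and evaluators were blinded, and the therapist would know the grouping". Two other sections bear on harms: the discontinuation criteria stop treatment after severe adverse events and keep the data already collected, and the ethics committee is named as the body that monitors trial data.

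**The concern.** A safety comparison needs a defined event, someone who asks about it, a place to record it and a tabulation by arm. The text supplies none of these. Its one harm section describes expectations and care, not measurement. The one person it names as dealing with discomfort is unblinded and has no part in data collection.

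The Discussion says the combination has not been studied before, so this trial would supply its first comparative safety evidence. If the text is followed as written, a statement that one therapy is as safe as another, or that combining them adds no harm, would have no planned data behind it. A later analysis plan could not repair this, because it cannot tabulate events that were never collected.

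**Working it through.** **Consistency check.** Each place where a harm variable could appear, and what is there:

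| Place in the protocol article | Content | Harm variable? |
|---|---|---|
| Abstract, Background | aim covers efficacy and safety | promised |
| Abstract, Methods | sEMG, NIH-CPSI; 3D ultrasound, SWE, SSR | none |
| Study design, T0 to T3 | the same five measures | none |
| Primary and Secondary outcome measures | definitions of those measures | none |
| Harm outcomes | expected risks; therapist judges and treats | none defined |
| Plans for assessment and collection of outcomes | timing of primary and secondary measures | none |
| Statistical methods | sEMG, NIH-CPSI, correlation, mediation, agreement | none |
| Criteria for discontinuing | severe adverse events stop treatment | noticed, but no recording stated |

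NIH-CPSI contains a pain and discomfort domain, but a total symptom score cannot separate pain caused by treatment from pain of the disease.

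**Size, from the protocol's own rate.** Inputs: about 15% perianal pain with myofascial release (Harm outcomes); 50 patients per arm (Sample size calculation); myofascial release given in two arms, myofascial and combined (Intervention).

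- Expected patients affected: 0.15 × 50 = 7.5 per arm, and 0.15 × 100 = 15 over the two arms.
- Wilson 95% interval for 15/100: 9.3% to 23.3%. If counted, the rate would be known to within about 6 points below and 8 points above.
- Zero events in 50 shockwave-only patients would still allow a true rate up to 7.1% (two-sided Clopper–Pearson limit). The very low risk the protocol expects could be checked only to that precision, and only if events are counted.

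**Why no power claim is made.** The documents give no perianal-pain rate for the shockwave arm. Zero is not safe to assume: every patient has internal palpation of the perineum and rectum with a wand (Intervention) and trans-rectal ultrasound (Secondary outcome measures). With 15/100 in the two myofascial arms, Fisher's exact test depends heavily on that unknown count:

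| Shockwave-arm events of 50 | p |
|---|---|
| 0 | 0.003 |
| 1 | 0.022 |
| 2 | 0.056 |
| 3 | 0.18 |

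For one myofascial arm against shockwave alone, 50 per arm, 15% against an assumed 1% to 5%, the power of Fisher's test runs from 0.64 down to 0.24. Pooling the two myofascial arms also says nothing about whether the combination adds harm. The useful product is therefore rates with intervals by arm, not a test.

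**The case against.** The strongest reply is that this is a condensed article. How adverse events are asked for, graded and tabulated is often left to the full protocol and the analysis plan. The SPIRIT schedule in Table 1 is not shown and could hold a harms row. This stands as a limit on certainty. It does not remove the point, because the article does give a harm section and full outcome and collection lists, and these do not deliver the comparison the abstract announces.

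A second reply is that safety appears as one phrase in the abstract, while the aims in Background and the questions in the Discussion concern efficacy, correlation and mechanism. That is fair. It is why removing the phrase is an acceptable alternative to collecting the data.

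Three stronger readings are tempting, and the text does not support them:

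- **Harms reach only the therapist and none would enter the data.** The text names no other route, but it does not exclude one. Severe events must be noticed, since they stop treatment. The ethics committee monitors data. The Intervention section shows researchers recording findings from the therapist's palpation.
- **The visit schedule would miss the events, and the 2-week call has no use but retention.** If pain lasts two treatments, onset at session 3 or 4 could still be present at T1, and onset at session 7 or 8 at T2. The stated purpose of the call is follow-up ("Participants were contacted by telephone 2 weeks after the last intervention to ensure the follow-up 4 weeks after the intervention"), but nothing restricts it to that.
- **The planned size is enough to show a difference in harms.** This holds only if the shockwave arm has almost no events.

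**Conclusion.** The point holds as an inconsistency between a stated aim and the data the text says will be collected. Safety is promised as a comparison, and no harm variable is defined, scheduled or analysed. Discomfort is handled by an unblinded therapist outside data collection, and severe events have no stated recording route. About 15 of 100 patients in the two myofascial arms would be expected to have the one harm the protocol quantifies. That figure rests on the 15% applying equally in both arms. The conclusion also assumes that Table 1 and any fuller protocol add no harm item, which cannot be seen here. A reader might infer that the trial can yield no safety information at all, and that goes too far. The efficacy comparisons are not affected. This should be corrected, but it is not fatal to the trial.

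**What to change.** Add a secondary outcome: the number and proportion of patients per arm with perianal pain, edema, capillary rupture or any other adverse event since the last contact.

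- **Collection.** One fixed question at T1, T2, the existing 2-week call and T3. Asking about the whole interval since the last contact removes any dependence on the event still being present at the visit.
- **Who asks.** The research assistant or, if the evaluator does it, only after that visit's efficacy measurements are complete. Perianal pain is the named effect of transrectal release, while the sham release is applied to the abdomen, so answers can hint at the arm. Asking before every session from session 2 is not advised: it would add up to 7 × 150 = 1,050 contacts and expose the evaluator repeatedly.
- **Therapists.** They pass events seen at sessions, including severe ones, to the data collector for recording. This keeps the blinding rule intact.
- **Reporting.** Rates with confidence intervals by arm for all treated patients, with no claim of equal safety from a non-significant test.

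If the sponsor does not want to collect this, remove safety from the stated aim.

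Cost: an amendment, one short form and a few minutes at contacts that already exist. Recruitment was under way when the article was written, so patients treated before the change would lack prospective harm data and should be reported separately.

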## Data collection and management

### Plans for assessment and collection of outcomes

Three groups of participants will be treated by trained therapists, and the intervention process will be strictly in accordance with the study protocol. The Primary outcome measurements will be carried out at T0, T1, T2, and T3. Secondary outcome measurements will be carried out at T0 and T3. Equipment used in the assessment, such as pelvic floor biofeedback electrostimulation, pelvic floor ultrasound, and sympathetic skin response devices, will be operated by the same researchers, and the type of equipment and the assessment site will remain the same.

### Plans to promote participant retention and complete follow-up

Once participants are enrolled in the study, the primary investigator will emphasize the importance of regular treatment for recovery. If participants can be evaluated at all stages of the treatment process, it will be free of charge. Funding will be detailed in funding statements. Participants were contacted by telephone 2 weeks after the last intervention to ensure the follow-up 4 weeks after the intervention.

### Data management and confidentiality

All data will be saved in an Easy trial database, a password-secured web-based clinical trial management system. All data is validated by having 2 individual persons enter data (double entry), and the database will check for inconsistency.

Participant data on paper obtained in the trial is kept under the participants’ ID numbers. The de-identified data will be used in the data management, and only authorized investigators will be able to access the paper documents. Publications from this trial will only contain de-identified information about trial participants. Data will not be freely available to other researchers but can be requested in a de-identified dataset to other researchers if found appropriate by the primary investigator.

### Sample size calculation

Previous studies showed that myofascial release therapy had notable effects [32] (corresponding to a Cohen’s *d* of about 0.5) on improving quality of life, prostate-related symptoms, and pain. The primary outcome will be the change in NIH-CPSI scores, the clinical response rate, and the remission rate as measured by the NIH-CPSI 4 weeks after the completed intervention. We assumed that extracorporeal shockwave combined with myofascial release therapy had similar effects on NIH-CPSI scores. A sample of 40 participants per group was computed by the G*power software to achieve a power of 60% and a level of significance of 5% and a 95% confidence level. To compensate for an estimated dropout rate of 25%, 150 participants will be ultimately required. (i.e., the number in each group is 50).

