#### Post-resting EMG

Patients will be required to rest again for 1 min to relax completely. We will then test the static pelvic floor muscle tone and measure the amplitude and coefficient of variation after exercise where a value greater than 4 μV suggests elevated post-resting pelvic floor muscle tone, which can easily lead to PFM ischemia and cause clinical conditions such as painful intercourse, urinary retention, and constipation.

(2)National Institutes of Health-Chronic Prostatitis Symptom Index (NIH-CPSI).

We used a questionnaire with 13 entries, consisting of 4 aspects: pain and discomfort symptom score, urinary symptom score, symptom impact score, and quality of life score, with a total score ranging from 0 to 43. The severity of CP/CPPS can be graded according to the total scores: mild (1–14), moderate (15–29), or severe (30–43).

The efficacy evaluation criteria are developed with reference to the National Institutes of Health-Chronic Prostatitis Symptom Index score. Clinical control is defined as no less than a 90% decrease in the NIH-CPSI score, obvious improvement as no less than 60% and less than 89% decrease, improvement as no less than 30% and less than 59% decrease, and ineffective as less than 30% decrease.

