### Statistical methods

Statistical analysts perform data analysis in a blind state. All statistics analyses will be performed using SPSS 25.0 for Windows (SPSS Inc., Chicago, IL, USA). All data will be entered into SPSS by the research assistant. A *p*-value of < 0.05 will be considered statistically significant. One-way (3 groups: single extracorporeal shockwave therapy vs single myofascial release therapy vs combined therapy) analysis of variances (ANOVA) with repeated measures will be performed to compare changes in sEMG assessment and NIH-CPSI scores between and within groups over different time points (i.e., T0-T2). A paired sample *t*-test was used to compare the differences in outcome indicators between groups at T2 and T3 to determine the long-term efficacy of each intervention. Post hoc analyses will be performed when any significant difference both between- and within-group is found in any of the outcome variables. Bonferroni correction will be used to adjust the alpha levels. Multilevel regression or a generalized estimating equation (GEE) will also be used as a sensitivity analysis to analyze the correlation between NIH-CPSI scores and the results of sEMG assessment of the pelvic floor muscle and the results of sympathetic skin response. Mediation analysis will examine the mediating effect of sEMG assessment at T1 on the relation between extracorporeal shockwave therapy and NIH-CPSI scores at T2. This study strictly controlled for gender, age, and BMI of the participants, which may affect the primary and secondary outcomes. The mean absolute difference (MAD) and standard error of measurement (SEM) will be used to evaluate inter-method reliabilities. Consequently, Bland–Altman plots will be used to investigate the agreement between NIH-CPSI and SSR. Since the two measurement results have different measurement units, a *Z*-score will be calculated based on the formula: *Z*-score = (observation value − mean value)/SD.

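### One power figure (60%, 40 per group), derived from a continuous effect on the NIH-CPSI score, stands for three named primary outcomes, two of which are rates to which it does not carry over

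*Protocol article*

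**What the plan says.** The section Sample size calculation lists three primary outcomes, to be measured 4 weeks after the intervention: "The primary outcome will be the change in NIH-CPSI scores, the clinical response rate, and the remission rate as measured by the NIH-CPSI". The effect is taken from earlier work on myofascial release, "corresponding to a Cohen’s *d* of about 0.5", and carried to the combined arm: "We assumed that extracorporeal shockwave combined with myofascial release therapy had similar effects on NIH-CPSI scores". From this the section obtains 40 per group with G*Power, and the target behind that number is given as "to achieve a power of 60% and a level of significance of 5% and a 95% confidence level". The section gives no response rate, remission rate or target difference in rates.

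The two rates are not defined under those names anywhere. The nearest text is the NIH-CPSI description at the end of the section Post-resting EMG, which grades percentage decrease in four categories. The top one reads "Clinical control is defined as no less than a 90% decrease in the NIH-CPSI score", and a decrease below 30% counts as ineffective.

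The Abstract and the section Primary outcome measures name sEMG and NIH-CPSI as primary and do not mention the two rates. In Statistical methods, the repeated-measures ANOVA "will be performed to compare changes in sEMG assessment and NIH-CPSI scores between and within groups over different time points".

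**The concern.** A standardised mean difference describes a comparison of means. A response or remission rate is a proportion, obtained here by cutting the percentage decrease in NIH-CPSI at a threshold. Its power depends on the rates in the two arms, and the article assumes none. Cutting a continuous score generally loses information, most of all when the cut lies far out in the tail, as a 90% decrease may.

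Because the paragraph calls all three outcomes primary and prints a single power, a reader will take 60% as the power of each. A non-significant response or remission rate could then be read as a primary result that had a 60% chance of detecting the assumed effect, when the chance was lower. This is separate from the three-arm and multiplicity questions: it already arises for one pairwise comparison at an unadjusted 5%.

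**Working it through.** **Inputs from the article.** d = 0.5; n = 40 evaluable per group; alpha 5%; stated power 60%. Neither the test nor its sidedness is given.

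**Step 1: reproduce the stated figure.** For a two-sample t-test the noncentrality is d × √(n/2) = 0.5 × √20 = 2.236, with 78 degrees of freedom.
- Two-sided 5%: power 59.8%. This matches the printed 60%.
- One-sided 5%: 71.6%.
- Two-sided at alpha/3: 42.1%.
- Three-group one-way ANOVA, N = 120: 67.6% (f = 0.25), 62.1% (f = 0.236), 49.3% (f = 0.204), 38.4% (f = 0.177).
- Between-group test in a repeated-measures ANOVA, f = 0.204, assumed within-subject correlation 0.7: about 59% with three measurements and 60.5% with four.

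The two-group t-test is the simplest match and needs no further assumption, but it is not the only possible one. Every match is a calculation for a continuous score.

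**Step 2: carry the same effect to a rate.** The comparator rate p1 is an assumption throughout.
- Normal latent score: p2 = Φ(Φ⁻¹(p1) + 0.5).
- Logistic latent score: odds ratio = exp(0.5 × π/√3) = 2.48.

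Both models apply d = 0.5 to the scale that is cut, which is itself an assumption. Power comes from exact binomial enumeration of the uncorrected chi-square test, n = 40 per group, two-sided 5%:

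| p1 | p2 normal | power | p2 logistic | power |
|---|---|---|---|---|
| 1% | 3.4% | 3% | 2.4% | 1% |
| 5% | 12.6% | 24% | 11.5% | 20% |
| 10% | 21.7% | 31% | 21.6% | 30% |
| 20% | 36.6% | 38% | 38.2% | 43% |
| 30% | 49.0% | 42% | 51.5% | 51% |
| 40% | 59.7% | 45% | 62.3% | 54% |
| 50% | 69.1% | 43% | 71.2% | 50% |
| 70% | 84.7% | 35% | 85.2% | 38% |

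Fisher's exact test is lower throughout; at p1 = 40% it gives 36% (normal) and 45% (logistic).

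**Step 3: read off the two outcomes.**
- Response, comparator 20–70%: about 35–45% under the normal model, up to about 54% under the logistic model. The gap to 60% is about 15–25 points (60 − 45 to 60 − 35), narrowing to about 6 points (60 − 54) in the most favourable case.
- Remission, if it means a decrease of at least 90% and the comparator rate is 1–10%: about 1–31%. At a comparator rate of 20%: about 38–43%.

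**Step 4: check whether the evaluable number changes the answer.** If all 50 per group were evaluable, the normal-model peak for response would be about 53%, and the t-test on the score would have about 70%. The gap remains.

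**The case against.** The strongest reply is that no printed number is wrong. The 60% reproduces, and the sentence before it speaks only of effects on NIH-CPSI scores, so the calculation was evidently made for the score. Sizing a trial on one continuous outcome and also reporting responder rates is common. This stands in part. A reader might infer an arithmetic error in the 60%, and the article does not support that. But that sentence limits only the effect assumption. The paragraph still gives the rates primary status and prints one power without saying which outcome it belongs to.

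Three further cautions stand:
- A reader might infer that the calculation certainly was a two-group t-test. The test is not named, and step 1 shows that a repeated-measures ANOVA with an assumed correlation also gives about 60%.
- A reader might take 45% as a ceiling for response, or 31% for remission. The first holds only under a normal latent score. The second rests on an assumed comparator rate of at most 10% and on equating remission with the category of at least a 90% decrease, an equation the article never makes.
- A reader might count the absence of a planned test for the rates as a fault. A condensed article may leave that to an analysis plan not shown here, so nothing is built on it.

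The primary-outcome lists also disagree: sEMG is primary in the Abstract and in Primary outcome measures but absent from the sample-size section, while the rates appear only in the latter. This adds to the point rather than answering it, since the list has to be settled before any power figure can be attached to it.

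**Conclusion.** The point holds as a matter of scope. The 60% is a correct figure for the NIH-CPSI score at d = 0.5 and 40 per group, and it does not describe the two rates named as primary beside it. In every case run at that d and n, power for a rate was below 60%, under both latent models and with either test. The direction is therefore firm over the cases examined, but the size is not. For response the shortfall runs from about 6 points to about 25 by the chi-square test. For remission it is larger if the outcome is a rare event, and the article gives neither a definition under that name nor a rate. The planned number of patients is not shown to be wrong for the score. The correction should be made, but it is one of wording and outcome status.

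**What to change.** In Sample size calculation, state that the 40 per group and the 60% apply only to the change in NIH-CPSI total score at T3, 4 weeks after treatment, and name the test used. List the response and remission rates as secondary outcomes, define each by the percentage-decrease categories already given with the NIH-CPSI description, and report them as between-arm risk differences with 95% confidence intervals. Make the list of primary outcomes agree with the Abstract and with Primary outcome measures.

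If the sponsor prefers to keep the rates primary, give each its own power from a two-proportion calculation using the sponsor's assumed rates. The percentages above are illustrations and should not be written into the protocol as limits.

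The cost is some rewording in the sample-size and outcome sections, with no change in the number of patients, visits or data. The price is that the rates lose primary status, or that a lower power is printed for them.
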